## Abstract

**Background:**

Mobile Technology and Incentives (MOTIVES) is a randomized pilot study of a mobile technology-based and behavioral economics-supported HIV prevention intervention. Behavioral economics (BE) uses financial incentives in a way that departs from the traditional focus on large monetary payments. Instead, BE suggests that relatively small “nudges” can effectively initiate and sustain behavior change. This pilot study examines the feasibility and acceptability of an HIV prevention intervention that uses text messages in combination with BE incentives to improve retention of HIV prevention information and increase frequency of HIV testing among Latino/a men who have sex with men (MSM) and transgender women (TGW). The pilot will also estimate mission-critical design parameters with point and confidence interval estimates of the intervention to inform a future, fully powered effectiveness study.

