### Design

We will pilot test the feasibility and acceptability of the intervention in a small RCT among 200 Latino/a MSM and TGW from Bienestar Human Services, Inc.’s (*Bienestar*) HIV testing sites. There will be approximately 90 MSM and 10 TGW in each arm. Participants will complete a survey at baseline, six, and 12 months. Participants will be randomized (procedures for this are described in detail below) into either the “information only” group (e.g. receiving text messages with HIV prevention information) or the “information plus” group (e.g. additionally receiving quiz questions that provide the possibility of winning prizes when answered correctly). Randomization will provide the comparison needed to identify the potential effect of winning a prize.

We will pilot the recruitment process with five participants. We will begin with a staggered enrollment process based on previous HIV testing data to identify the highest volume *Bienestar* sites. During the study we are collecting quantitative data on both primary outcomes (e.g. HIV knowledge and frequency of testing behavior) and secondary outcomes (e.g. HIV status).

All participating institutions received approval from their respective Institutional Review Boards and a certificate of confidentiality has been obtained from the National Institute of Mental Health. Any protocol modifications will be submitted to the IRBs for review, and participants will be informed if warranted. The trial was registered on 5 May 2017 with the ClinicalTrials.gov registry (NCT03144336).

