At enrollment, we will take several steps to ensure the confidentiality of participants related to text message communication. For example, as mentioned above, MOTIVES HIV testers will instruct participants how to properly use the SMS system, maintain privacy on their device, and delete SMS messages from their mobile device. Finally, study staff will call the participant (either using an office line or using the *67 feature to make a protected call using their personal cell phone) to confirm that study staff has the correct cell phone contact number for the participant. At this time, participants will receive a $15 gift card.

After participating in the baseline survey and receiving their gift card, participants will be randomized using computer allocation by the study PI. The goal is to ensure that the randomization process does not influence responses to the baseline survey (e.g. responding more quickly if they were not chosen for the prize drawing group and feeling disappointed and less invested in the study). The study design was guided by its purpose as a pilot trial; we used a 1:1 randomization as it provides the greatest power for testing effectiveness in preparation for a future definitive RCT. Hereafter we will refer to the two groups as: (1) Information plus group (intervention group); and (2) Information only group (control group). HIV testers will also reaffirm that assignment is completely random and not based on the personal characteristics of any individual client. RAND study staff will explain to testers why randomization is so important, underscoring that only with their help can we actually understand if the intervention works. If testers select participants based on their own judgment of who is most in need of the intervention (e.g. they think a client appears particularly poor and would really appreciate having gift cards), we would not be able to collect accurate data. If a certain type of client is consistently included in the information plus reminders group, we will not be able to determine if the intervention works with everyone or just with a particular type of person.

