As summarized in Table 1, we will explore a range of variables. The independent variables include control variables not only to improve efficiency, but also to learn about the paths through which the intervention works and to identify subgroups that are likely to particularly benefit from the intervention. Furthermore, potential mediators of behavior, such as level of acculturation, may result in improved provider communication and hence information access. For example, some people may want to avoid being seen at a clinic or HIV testing site, but for people who can communicate with providers more easily, this cost is close to zero, and their behavior may not be altered through the intervention. We can test this effect by forming an interaction between the acculturation measure and the intervention. With respect to the dependent variables, the primary outcomes include HIV knowledge and frequency of HIV testing; the secondary outcomes include HIV infection. Continuous variables will be assessed for normality and transformed if needed. Analyses will be conducted for the whole sample as well as for Latino/a MSM and TGW separately to arrive at the potentially differential impact of the MOTIVES intervention for these two groups. Logit estimation will be used for binary outcome measures.

We will impute missing data for some variables if an individual is still enrolled. When participants drop out, we will fit multiple logistic regression models to assess whether this dropout is random. If it is not, we will construct “non-response” weights using logistic regression that correct for dropout. Analyses will reflect these design effects in the calculation of standard errors and tests of significance.

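### Differential impact in MSM and TGW is to be judged from separate analyses with about 10 TGW per arm and no arm-by-group contrast, so reading them by significance can suggest a difference where none exists

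*Protocol article*

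**What the plan says.** The Design section describes a pilot "in a small RCT among 200 Latino/a MSM and TGW" and adds: "There will be approximately 90 MSM and 10 TGW in each arm". Allocation is equal (MOTIVES intervention section).

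On subgroups, the Data analysis section states: "Analyses will be conducted for the whole sample as well as for Latino/a MSM and TGW separately to arrive at the potentially differential impact". The separate analyses are thus the stated route to a conclusion about difference in effect. Earlier in the same paragraph, for acculturation, the article takes another route: "We can test this effect by forming an interaction between the acculturation measure and the intervention". It also gives finding the subgroups most likely to benefit as one reason for its choice of variables.

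The outcomes concerned are the main ones: "the primary outcomes include HIV knowledge and frequency of HIV testing". Testing also appears as a yes/no variable, whether a test occurred within three months. The closing sentence on missing data expects formal testing: "Analyses will reflect these design effects in the calculation of standard errors and tests of significance". The abstract, by contrast, speaks of "point and confidence interval estimates of the intervention to inform a future, fully powered effectiveness study". No alpha, effect size, testing rate, power figure or rule for declaring a differential impact is given.

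**The concern.** A differential effect is a contrast between two treatment effects. Two within-group analyses set side by side do not supply that contrast or its uncertainty unless someone subtracts one from the other and gives a standard error. The usual shortcut is to see which group reached significance. That mostly reflects group size when one group is nine times the other: the MSM analysis can have good power while the TGW analysis has almost none, even if the intervention works equally well in both.

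At stake is what the pilot says about the smaller group. The article wants the results to help tailor the intervention for a later trial, and a null result in about 20 TGW could be misread as evidence of no benefit.

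**Working it through.** **Inputs from the article.** 90 MSM and 10 TGW per arm; the total 2 × (90 + 10) = 200 agrees with the stated sample size. There is no power calculation to reproduce.

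**Assumptions (not in the article).** Two-sided alpha 0.05; no dropout, with 20% as a sensitivity case; the same true effect in both groups; and the testing rates and standardised effects listed below.

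**1. Binary outcome.** Exact Fisher power in each group, by enumerating all outcomes. The groups are independent, so

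P(significant in MSM, not in TGW) = power_MSM × (1 − power_TGW).

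| Control v intervention | Power, MSM (n = 90) | Power, TGW (n = 10) | MSM only |
|---|---|---|---|
| 40% v 50% | 0.216 | 0.020 | 21% |
| 30% v 40% | 0.243 | 0.020 | 24% |
| 40% v 55% | 0.448 | 0.033 | 43% |
| 30% v 45% | 0.498 | 0.034 | 48% |
| 40% v 60% | 0.706 | 0.053 | 67% |
| 30% v 50% | 0.749 | 0.054 | 71% |
| 30% v 60% | 0.977 | 0.123 | 86% |

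For example, at 40% v 60%: 0.706 × (1 − 0.053) = 0.669. For 10-point effects the usual result is non-significance in both groups, about 75% of trials. Using Pearson's test in MSM, and Fisher or Pearson in TGW, moves the figures only modestly: 28-29% at 30% v 40%, and 66-72% at 40% v 60%.

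**2. Continuous outcome, such as the knowledge score.** Two-sample t-test with noncentrality d√(n/2). At d = 0.5 this is 0.5 × √45 = 3.35 for MSM and 0.5 × √5 = 1.12 for TGW. The powers are 0.916 and 0.184, and 0.916 × 0.816 = 0.747.

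| Common effect d (SD) | MSM | TGW | MSM only |
|---|---|---|---|
| 0.2 | 27% | 6% | 25% |
| 0.3 | 52% | 9% | 47% |
| 0.4 | 76% | 13% | 66% |
| 0.5 | 92% | 18% | 75% |
| 0.8 | about 100% | 40% | 61% |
| 1.0 | about 100% | 56% | 44% |

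The last column exceeds one half only for d between about 0.32 and 0.92, with a peak of about 75% near 0.53. With 20% dropout (72 and 8 per arm) the range is about 0.36 to 1.05.

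**3. Precision.** Normal approximation, with rates of 50% as the widest case:
- TGW risk difference: 1.96 × √(0.5/10) = 0.438, about 44 points.
- Interaction (difference between the two risk differences): 1.96 × √(0.5/10 + 0.5/90) = 0.462, about 46 points.
- Interaction in SD units: 1.96 × √(2/90 + 2/10) = 0.92. A difference of 2.80 × 0.471 = 1.32 SD would be needed for 80% power, and power for a true difference of 0.5 SD is 19%.

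**4. What the interaction test does under a common effect.** In 20,000 simulated trials it was significant in 5.3%, 4.8% and 4.7% at d = 0.3, 0.5 and 0.8. Its error rate therefore does not depend on the size of the shared effect, unlike the side-by-side reading.

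**The case against.** The strongest defence is that the article never says it will compare significance between the groups. It is a feasibility pilot, the abstract promises estimates with confidence intervals, and the subgroup sentence is hedged. Read as estimates, a TGW interval of about ±44 points shows imprecision rather than absence of effect. The difference between two group-specific estimates is also exactly the arm-by-group coefficient of a saturated model, so separate analyses do not make the contrast impossible. And the interaction is itself too imprecise to settle anything.

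Much of this stands, and it limits the point. Three stronger readings are tempting and are not supported:
- A reader might infer that the false contrast will appear in most trials, or is built into the design. That depends on an effect size the article does not state; for a 10-point difference it appears in fewer than a quarter of trials.
- A reader might infer that adjusted models in 20 TGW cannot be fitted. The number of covariates is not given and no such failure has been shown; imprecision is all that can be claimed.
- A reader might infer that the later trial would be steered away from TGW. No passage says so, and the article's one numerical criterion concerns participation.

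What the defence does not remove is that the article picks a method for this question, leaves out the contrast and its interval, and plans significance tests and a search for subgroups that benefit. It uses the better tool for acculturation. This is a stated choice, not a detail left to an unseen analysis plan.

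**Conclusion.** The concern holds in conditional form. The planned separate analyses, with no arm-by-group contrast, are a poor means of judging differential impact with 90 versus 10 per arm. If they are read by significance at two-sided 0.05, an identical effect yields an MSM-only finding in about 21-24% of trials at 10 points, 67-71% at 20 points and 86% at 30% versus 60%. On a continuous outcome this happens in more than half of trials only for common effects of about 0.32 to 0.92 SD. Alpha, rates and effect sizes are assumptions, and so is the reading by significance. However the results are read, half-widths of about 44 points (TGW) and 46 points (interaction) mean that the pilot can neither establish nor exclude a differential effect. The feasibility and acceptability aims are unaffected.

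**What to change.** In the Data analysis section:
- Assess differential impact with one model containing arm, group (MSM or TGW) and arm-by-group. Report the interaction with its 95% CI and label it exploratory.
- Show MSM and TGW results as estimates with confidence intervals, with TGW descriptive and without p-values.
- State that neither a differential effect nor absence of effect in TGW will be inferred from separate p-values.

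The cost is wording only, with no added participants or data. The downside is a weaker subgroup claim. The change prevents a false contrast but does not make the pilot informative about a difference in effect.

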### Characteristics of participants

Latino/a MSM and TGW clients who present at *Bienestar* HIV testing sites will undergo risk reduction counseling and rapid HIV testing following usual testing site protocols. Clients who test positive for HIV will be linked to services per the standard of care at *Bienestar*. Clients who test negative for HIV will be asked if they have interest in participating in the MOTIVES study. Those who express interest will be screened for the following eligibility criteria: own or have regular access to a smartphone; self-identify as MSM or TGW; self-identify as a Latino/a; aged ≥ 18 years; fluent in English or Spanish; able to provide contact information for at least three tracking mechanisms (e.g. cell phone, email, address, friend’s contact); and testing HIV negative.

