We will conduct group comparisons at six-month intervals to assess the intervention’s short- and mid-term effects. In addition to simple group comparisons at each time point, we will exploit the longitudinal nature of the data by using repeated-measures and time-series techniques. This approach will allow us to examine whether self-reported sexual behaviors persist or decline similarly between the two groups. Repeated measures models will be fitted using Xtreg in the software package Stata. We will use an Analysis of Covariance (ANCOVA) framework to test for group differences, controlling for relevant client characteristics that are found to differentiate the groups at baseline in order to improve the precision that would result from a simple Analysis of Variance (ANOVA) on randomly assigned individuals. For analyses with the dichotomous variables such as HIV testing within a three-months period, we will use a non-parametric McNemar’s test and an analogous multiple logistic regression to control for covariates to assess group differences.

As with any randomized trial (that eliminates selection bias), the first and most direct way to evaluate the impact of an intervention is a simple comparison *D* of the group means in adherence levels.$$ D=E\left[{Y}_i^T\left|T\right.\right]-E\left[{Y}_i^C\left|C\right.\right] $$, *E[Y]* indicates the expected outcome in intervention group *T* and control group *C*.Taking into account the longitudinal nature of the data, this can be written as: $$ D=E\left[\Delta {Y}_i^T\left|T\right.\right]-E\left[\Delta {Y}_i^C\left|C\right.\right] $$In small samples efficiency can be improved by controlling for differences in control variables between the groups that may arise due to chance as discussed above. The approach can be implemented in a regression framework (and again, can be implemented in differences rather than levels): *Y*_*i*_ = *α* + *βT* + *δX*_*i*_ + *ε*_*i*_

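### Logit is fixed for all binary outcomes and repeated in about 20 TGW; for HIV infection, and for covariate-adjusted TGW models, it will often give no finite odds ratio

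*Protocol article*

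**What the plan says.** The Data analysis section of the protocol article sets the method for binary outcomes without exception: "Logit estimation will be used for binary outcome measures". Shortly before, it sets the populations: "Analyses will be conducted for the whole sample as well as for Latino/a MSM and TGW separately". It also says that "the secondary outcomes include HIV infection".

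For dichotomous variables, with HIV testing in a three-month period as the example, the same section says "we will use a non-parametric McNemar’s test and an analogous multiple logistic regression to control for covariates to assess group differences". The covariates are client characteristics found to differ between the groups at baseline, and their number is not given. An interaction between arm and acculturation is also planned.

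The sizes come from the Design section: a "small RCT among 200 Latino/a MSM and TGW", in which "There will be approximately 90 MSM and 10 TGW in each arm". On allocation, the MOTIVES intervention section says "we used a 1:1 randomization". On HIV status at entry, Characteristics of participants says "Clients who test negative for HIV will be asked if they have interest in participating in the MOTIVES study", and a negative test is an eligibility criterion.

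No exact, penalised or other sparse-data method is named.

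**The concern.** A maximum-likelihood logit gives a finite odds ratio for arm only if both arms contain events and non-events. With covariates it also needs the outcome not to be perfectly split by some combination of them, which becomes hard to avoid in about 20 people. Two planned uses come close to these limits: HIV infection in people who all start negative, and any covariate-adjusted binary outcome in TGW.

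If the wording is followed, the HIV-infection odds ratio may be zero, infinite or undefined, with a meaningless Wald interval. The adjusted TGW result would depend on which covariates were dropped to make the model run. The article wants the TGW analysis to show whether the effect differs between groups, and it lists the proportion with a positive rapid test among the parameters needed to design the next trial. An odds ratio that cannot be estimated serves neither purpose.

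**Working it through.** The article states no power, incidence, testing rate or dropout, so there is no figure of its own to reproduce. The group sizes are consistent: (90 + 10) × 2 = 200.

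**Inputs from the article:** n = 100 per arm in the whole sample and n = 10 per arm in TGW; all HIV-negative at entry; 12 months of follow-up.

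**Assumptions:** annual HIV incidence r of 1% to 5%; three-month testing rate of 50% or 70% in controls with a true odds ratio of 2; 0, 4 or 6 covariates. The prevalences in the Background (40% and 17%) are not 12-month event rates and are not used.

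**1. HIV infection: chance that at least one arm has no events.** With equal rates, P = 1 − [1 − (1 − r)^n]².

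Worked case, n = 100 and r = 0.01: 0.99^100 = 0.366, so P = 1 − 0.634² = 0.598.

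| r | Whole sample, 100 per arm | TGW, 10 per arm |
|---|---|---|
| 1% | 60% | 99% |
| 2% | 25% | 97% |
| 3% | 9% | 93% |
| 4% | 3% | 89% |
| 5% | 1% | 84% |

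If dropout leaves 80 per arm, the whole-sample figures at 1%, 2%, 3% and 5% become 69%, 36%, 17% and 3%. If the intervention halves the rate with 100 per arm, they become 75%, 45%, 26% and 9% (control rates shown).

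**2. HIV infection: the estimates that are finite.** This is the exact mean of the unadjusted log odds ratio, given that it is finite, with 100 per arm and a halved rate.

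| Rates | True log OR | Mean when finite | Share of truth |
|---|---|---|---|
| 1% v 0.5% | −0.698 | −0.179 | 26% |
| 2% v 1% | −0.703 | −0.350 | 50% |
| 3% v 1.5% | −0.708 | −0.494 | 70% |
| 5% v 2.5% | −0.719 | −0.680 | 94% |

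The finite estimates are pulled toward the null.

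**3. HIV testing in TGW, no covariates.** An arm with rate p gives no finite estimate with probability f(p) = p^10 + (1 − p)^10. The model fails with probability 1 − [1 − f(p_C)][1 − f(p_T)].

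- Control 50%, so intervention 66.7%: f = 0.0020 and 0.0174, failure 1.9%. Mean finite log OR 0.74 against 0.69.
- Control 70%, so intervention 82.4%: f = 0.0283 and 0.1435, failure 16.8%. Mean finite log OR 0.57 against 0.69.

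**4. HIV testing in TGW, with covariates.** These are simulated samples of 10 v 10 with standard-normal covariates unrelated to the outcome, with separation checked by linear programming. The ranges are over repeated runs of 800 to 1,500 samples.

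| Covariates | Control rate | Separated | Mean finite log OR | Median (true 0.69) |
|---|---|---|---|---|
| 4 | 50% | 6–7% | 1.03–1.25 | 0.90–0.92 |
| 4 | 70% | 27–28% | 0.75–1.04 | 0.70–0.81 |
| 6 | 50% | 23% | 1.42 (one run) | 0.97 |
| 6 | 70% | 50–52% | 1.04 (one run) | 0.91 |

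The means move between runs because a few nearly separated fits dominate them. The medians show less bias, and almost none in some runs with 4 covariates at 70%. A separate run used 3 covariates that do predict the outcome, with rates of 50% v 70%: 8.5% of fits separated, and the mean was 1.55 and the median 1.27 against a true 0.85.

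**The case against.** The strongest reply is that much of what is needed is already planned. The Data analysis section calls the simple difference in group means the most direct evaluation. For a binary outcome that is the unadjusted risk difference, which always exists. The section also lists proportions for dichotomous endpoints, including a positive rapid test, as design parameters. This stands: the plan would not leave these outcomes without any finite summary. It does not remove the point, because the logit is still the stated method for binary outcomes and no exception is made. McNemar's test does not fill the gap either, since it compares paired proportions and not independent arms.

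A second reply is that a sparse-data fallback belongs in an analysis plan that is not shown. That would hold if the article were silent, but it names the method and the subgroups.

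A third is that the size of the problem rests on assumptions. This also stands. At about 5% incidence the whole-sample HIV model, unadjusted and with equal rates, nearly always gives a finite estimate. The number of covariates is not stated, and with none the TGW testing model shows little bias at a 50% control rate and some shrinkage at 70%.

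A reader might infer that the plan will produce large, spurious odds ratios throughout. The figures do not support that. Finite whole-sample HIV estimates shrink toward the null in the unadjusted calculation. In simulated TGW testing models, Wald 95% intervals from finite fits covered the truth in about 97% or more of cases. Those results would be very imprecise, but not falsely decisive.

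**Conclusion.** The concern holds in limited form. For HIV infection in TGW, the stated method fails in 84% to 99% of trials over the assumed 1% to 5% incidence. In the whole sample it fails often at 1% to 2% (60% and 25%), and seldom at 4% to 5% (3% and 1%) if rates are equal and nobody drops out. For HIV testing in TGW the unadjusted logit is usable at mid-range rates, with about 2% failures at a 50% control rate and 17% at 70%. It becomes unreliable once several covariates enter, by an amount that depends on a covariate count the article does not give. No single bias percentage should be quoted.

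It would be wrong to infer that the trial's main purpose is at risk. One secondary outcome and one subgroup of a pilot are affected. The feasibility and acceptability aims are not, and nothing here counts against logit for HIV testing in the whole sample or in MSM. The change is worth making because it is nearly free.

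**What to change.** Replace the general logit sentence with three rules.

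- Restrict covariate-adjusted logit to HIV testing in the whole sample and in MSM.
- For HIV infection, report counts and proportions per arm with Clopper-Pearson 95% intervals, or person-time rates with exact Poisson intervals, without covariates.
- For binary outcomes in TGW, report counts and the unadjusted risk difference with a score or exact interval. If a model is wanted, use Firth penalised logit with arm only.

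Firth's estimate is always finite. With 10 per arm and rates of 50% v 70%, its mean log odds ratio is 0.850 against a true 0.847. It cannot create information: for HIV infection at 1% v 0.5% with 100 per arm, its mean is −0.384 against −0.698. That is why counts and exact intervals are preferred for infection.

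The cost is a few sentences of analysis wording. Covariate adjustment is lost for these outcomes. The intervals will be wide, which reflects how little 20 people or a handful of infections can show.

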### Measures: health outcomes

Enrolled participants respond to a baseline assessment after they have completed screening and consent. The MOTIVES HIV tester reads the baseline survey to participants to guarantee understanding by clients across a range of literacy levels. Together the screening and consent processes take approximately 15 min to complete; the baseline survey takes approximately 30 min. Participants will complete a shortened six-month survey via response to a link sent to them on their phone. If participants cannot complete the six-month survey on their own, the Study Coordinator will offer to meet them at a local library of their choice and provide a tablet to complete the survey. However, we expect this circumstance be the exception rather than the rule. Participants will receive a $15 gift certificate via text after completing the six-month survey.

The 12-month follow-up survey will have fewer questions and will be completed after the intervention is over, Thus, completing the questions at a *Bienestar* testing location will not confound the outcome of interest. Participants will receive a $15 gift card for participating in the final survey. For those who do not complete their HIV test for that period, we will send a text message reminder to complete the final survey at *Bienestar*. Table 1 describes when each set of questions will be asked.

**Table 1 Tab1:** Health outcomes and measures of interest

Outcome	Instrument	Data collection timepoint
Primary Outcome		
HIV knowledge	Carey MP, et al. Development and psychometric evaluation of the brief HIV knowledge questionnaire (hiv-kq-18). AIDS Education and Prevention. 2002; 14: 174-184.	enrollment, 6 & 12 months
HIV testing behaviors	Extracted from *Bienestar* clinic data	
Secondary Outcomes		
HIV infection	Oraquick/Orasure	enrollment, 3, 6, 9 and 12 months
Covariates of Interest		
Socio-demographic information	Based on previous *Bienestar* questionnaire	enrollment & 12 months
Acculturation	Marín, G et al. Development of a short acculturation scale for Hispanics. Hispanic Journal of Behavioral Sciences. 1987; 9:183–205.	
Mental health	Kessler, RC et al. Short screening scales to monitor population prevalences and trends in non-specific psychological distress. Psychological Medicine. 2002; 32: 959-956.	
Substance abuse	Carballo-Diéguez, A et al. Microbicide Safety and Acceptability in Young Men: Baseline Behavioral Questionnaire. 2010.	

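### Dropout is corrected only if a logistic model finds it non-random; at about 100 per arm that check is weak for moderate patterns, so survey estimates may stay biased

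*Protocol article*

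**What the plan says.** The Data analysis section of the protocol article sets out a sequence. For people still in the study: "We will impute missing data for some variables if an individual is still enrolled". For those who leave: "When participants drop out, we will fit multiple logistic regression models to assess whether this dropout is random". Then: "If it is not, we will construct “non-response” weights using logistic regression that correct for dropout". No outcome is named as inside or outside this rule.

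The same section lists several analyses of group differences: a simple difference in means, a difference in mean changes, a regression form of each, repeated-measures models fitted with Xtreg, and ANCOVA "controlling for relevant client characteristics that are found to differentiate the groups at baseline". None is named as primary.

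Table 1 (Measures: health outcomes) gives the two primary outcomes different sources. HIV knowledge is a questionnaire score taken at enrolment, 6 and 12 months. HIV testing behaviour is "Extracted from *Bienestar* clinic data".

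On size, the Design section describes a "small RCT among 200 Latino/a MSM and TGW" and adds: "There will be approximately 90 MSM and 10 TGW in each arm".

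**The concern.** Once dropout is judged random, nothing is done about it: weights are not built, and imputation does not reach people who have left. The decision therefore depends on a test, and failing to find a pattern is not evidence that none exists. The test can only use what was observed, so it says nothing about dropout driven by the knowledge score that was never collected.

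Dropout that differs by arm is plausible here. Only one arm receives quizzes and prize drawings, and the Background and MOTIVES intervention sections expect incentives to help retention.

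Two things are at stake: the knowledge comparison, and the means and standard deviations that the pilot is meant to hand to the definitive trial. A lesser issue is scope. The rule is not confined to survey outcomes, although testing can be read from clinic records for someone who has stopped answering surveys.

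**Working it through.** The article gives no dropout rate, significance level or covariate list for this check, so there is no figure of its own to reproduce. The inputs from the article are 200 participants, 1:1 allocation and hence about 100 per arm. Everything else below is an assumption.

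**1. Power to see a dropout gap between arms** (two-sided 5%, n = 100 per arm)

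Power = Φ[(|p1 − p2| − 1.96·se0)/se1], with se0 = √(p̄(1 − p̄)·2/n) and se1 = √((p1(1 − p1) + p2(1 − p2))/n).

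- 10% v 20%: se0 = √(0.1275 × 0.02) = 0.0505; se1 = √(0.25/100) = 0.0500; Φ(0.02) = 51%.
- 15% v 25%: se0 = √(0.16 × 0.02) = 0.0566; se1 = √(0.315/100) = 0.0561; Φ(−0.19) = 42%.
- 20% v 30%: se0 = √(0.1875 × 0.02) = 0.0612; se1 = √(0.37/100) = 0.0608; Φ(−0.33) = 37%. Reaching 80% would need 294 per arm.

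The same formula gives 13% for 20% v 25%, 66% for 20% v 35%, 80% for 10% v 25% and 88% for 20% v 40%. Among transgender women alone, at 10 per arm, 20% v 40% has 16% power.

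**2. When a missed pattern biases the arm difference** (simulated trials, 100 per arm, no true effect, baseline-outcome correlation 0.5, 25–30% dropout; the check is an overall likelihood-ratio test at 5% on arm, baseline value and three irrelevant covariates)

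| Dropout depends on | Flagged | Bias of unadjusted difference (SD) | After baseline adjustment (SD) |
|---|---|---|---|
| arm only (log-OR 0.53) | 24% | about 0 | about 0 |
| baseline, equally in both arms (log-OR 0.4 per SD) | 43% | about 0 | about 0 |
| baseline, in one arm only (log-OR 0.4 to 0.7) | 13–34% | −0.05 to −0.09 | about 0 |
| baseline, in opposite directions by arm | about 6% | −0.10 to −0.15 | about 0 |
| the unseen outcome, in opposite directions by arm | about 6% | −0.20 to −0.30 | −0.15 to −0.23 |

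The 6% flag rate is essentially the test's false-alarm rate, so the worst patterns are invisible to it. If any single one of the five coefficients below 0.05 counted as a flag, false alarms alone would reach 1 − 0.95⁵ = 23%.

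**3. One scenario at about 20% dropout**

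The dropout logit is −1.4 − 0.6x in the control arm, where x is standardised baseline knowledge, and −1.6 in the intervention arm. The check (arm and baseline knowledge) flags 38–39% of trials. In the unflagged trials the completers' difference is off by 0.05 to 0.06 SD. With about 80 completers per arm the standard error is √(2/80) = 0.158, and 0.05/0.158 = 0.32, about a third. The completers' change-score difference is off by about 0.065 SD in the opposite direction. Adjusting for baseline knowledge leaves under 0.01 SD.

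**4. Does always weighting suffice?**

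No. In scenario 3, main-effects weights applied in every trial leave 0.05 SD, as the two-step rule does. Adding an arm-by-baseline term to the weight model brings this under 0.01 SD.

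**5. Single-arm parameters**

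If dropout depends on baseline equally in both arms (second row of the table, 25.6% dropout), the arm difference is safe but each arm's mean is not. To first order, the completers' baseline mean shifts by 0.4 × 0.256 = 0.10 SD, and the outcome mean by 0.5 × 0.10 = 0.05 SD.

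**The case against.** The strongest reply is that the damage is conditional and partly met elsewhere. A reader might infer that the rule usually leaves a biased comparison. The article does not support that: it states no dropout rate, and the arm difference is biased only if dropout relates to the outcome differently by arm. A pure gap between arms, the case for which power is easiest to quote, does no harm to the comparison when missed. Power is also adequate for some larger gaps. All of this stands.

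The planned repeated-measures models also matter. In the scenario of step 3, a random-intercept model using all enrolment data reduced the bias in unflagged trials from 0.053 to 0.010 SD. But the article does not say whether the models use random or fixed effects and does not make them primary. It also limits ANCOVA covariates to characteristics that happen to differ at baseline, so baseline knowledge may not enter.

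A reader might further infer that survey non-completers are removed from the testing outcome. No sentence says so, and dropout is not defined as survey non-response; the text merely leaves that reading open. Nor may a missing record be read as no test. Bienestar is one organisation, and its records need not capture tests done elsewhere.

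Finally, this is a pilot whose effect estimates are preliminary. That limits the consequence, but parameter estimation is one of its stated purposes.

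**Conclusion.** The point holds in a limited form. The article fixes a rule under which dropouts are corrected only after a positive test. At this sample size the test has about 37–51% power for 10-point gaps between arms, over assumed rates from 10% v 20% to 20% v 30%. It has essentially none for outcome-dependent dropout in opposite directions by arm. A negative result therefore does not justify leaving dropouts uncorrected.

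The comparison may stay biased, by 0.05 to 0.06 SD in the 20%-dropout scenario and by more under stronger or outcome-dependent mechanisms. Single-arm means can be biased even where the comparison is not. These sizes rest on the assumed dropout rates, the 5% level, the correlation of 0.5 and the chosen mechanisms. The scope question for testing frequency is a clarification rather than a demonstrated error. Overall this is a moderate weakness that should be fixed, not one that undermines the trial.

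**What to change.** - **Survey outcomes such as HIV knowledge:** stop using the logistic check as the trigger; it may stay as description. Name one primary method, applied whatever dropout looks like, that includes arm and the enrolment value of the outcome: a likelihood-based repeated-measures model, baseline-adjusted ANCOVA, or multiple imputation. Always-on main-effects weights alone are not enough.
- **Sensitivity:** add an analysis that lets dropout depend on the unseen outcome, with the departure allowed to differ by arm, because baseline adjustment only reduces that bias.
- **Testing frequency:** state that every randomised participant is analysed from clinic records whether or not surveys were completed. Define the outcome as tests recorded at Bienestar, and note that tests elsewhere may be missed.

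The cost is a change of analysis wording, slightly more analysis work and possibly slightly wider intervals. No extra data collection is needed.
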